### Who will take informed consent? {26a}

Written informed consent is gathered from participants. During the enrollment visit, trained research staff explain the study procedures, risks, and strategies to minimize risk during the informed consent process.

### Additional consent provisions for collection and use of participant data and biological specimens {26b}

In addition to providing informed consent, enrolled participants are required to provide permission for the researchers to use their personal health information for the study. Specifically, participants are asked to authorize the release of their HIV/AIDS treatment information (i.e., lab reports of HIV viral load, HIV care medical visit dates) from the community-based FQHC for the research.

### Interventions

#### Explanation for the choice of comparators {6b}

The comparator in this trial is the community-based FQHC’s existing Ryan White medical and coordinated case management services as usual. Their UC includes outpatient/ambulatory medical care, AIDS Drug Assistance Program (e.g., through Medicare, Medi-Cal), oral healthcare, early intervention services, mental health services, health education, medical nutrition therapy, medical case management, substance use disorder outpatient services, and support services (e.g., emergency financial assistance, food pantry, housing services, medical transportation, and legal services).

#### Intervention description {11a}

The PATH intervention integrates two theoretically grounded interventions developed by the team of investigators—a peer navigation intervention and an mHealth tool—with the goal of amplifying the impact of peer navigation on viral suppression among Hispanic and Black PLWH.

The peer navigation component is informed by our prior research developing “Conexiones Saludables” (“Healthy Connections” in Spanish; “Conexiones” for short), which is a theory-based intervention including modularized training for peer navigators to build core competencies in supporting marginalized PLWH [29, 30]. Peer navigators undergo 3 weeks of daily modularized training (15 modules total). Conexiones also included peer-delivered “peer empowerment sessions” designed to promote information, motivation, and behavioral skills (self-efficacy) in HIV care engagement and ART adherence, especially in the context of co-occurring conditions like substance use and mental health conditions. Sessions are conducted on a one-on-one basis between the participant and their assigned peer navigator and are delivered monthly over approximately 6 months using motivational interviewing techniques to facilitate intrinsic motivation for behavior change [31]. The design of Conexiones was based on the Situated Information, Motivation, and Behavioral skills (IMB) Model [32], which outlines how behavioral skills to engage in HIV care and adhere to ART should be situated to one’s specific socio-structural context, such as substance use or cultural norms in order to enact behavior change (e.g., ART adherence) [32, 33]. For example, providing information about ART adherence strategies aligned with drug use patterns, understanding sociostructural factors, such as intersectional stigma and discrimination, affecting motivation to engage in healthcare and treatment, and developing behavioral skills, such as self-efficacy, to maintain ART adherence even in a context of substance use stigma in the healthcare setting. In addition to the Situated-IMB Model, Conexiones was also founded in the Theory of Triadic Influence [34], a multilevel Social Cognitive theory [35] that hypothesizes three “streams of influence” (individual, social, and structural) which may act simultaneously to affect self-efficacy to engage in healthy behavior. Operationalized to the health behavior context of Hispanic and Black PLWH, the streams of influence most relevant to PATH include individual-level barriers (being a racial/ethnic minority, substance use) and socio-structural level barriers, such as or substance use stigma or medical mistrust, that decrease both Hispanic and Black people’s engagement in health and HIV care [18–20, 36–39]. Conexiones pilot data demonstrated improvement in HIV care continuum outcomes among marginalized Hispanic PLWH, such as people who use and/or inject drugs, in the US-Mexico border region [29, 30, 40].

The mHealth component of PATH is informed by “LinkPositively,” a mobile-optimized web application (or “webapp”) aimed at improving engagement in the HIV care continuum [41]. The LinkPositively intervention includes interactive features that were based on the IMB model [32, 42]. For example, the webapp incorporated information relevant to HIV self-management (educational and self-care tips feature), motivational enhancements (social support via a feed that participants can post to and reply to comments from other participants and gamification features), and behavioral skills (ART self-monitoring feature) to improve ART adherence. Based on focus group and community feedback, adaptations were made to the original Conexiones and LinkPositively interventions to make them more culturally tailored for both Hispanic and Black PLWH (e.g., creating English and Spanish language versions, using images that both Hispanic and Black participants may identify with).

Applying the theoretical foundations that informed the PATH peer navigation and mHealth components, Fig. 1 summarizes how PATH is hypothesized to target multiple psychological and social mechanisms of action, which should ultimately lead to a potent impact on HIV care outcomes among Hispanic and Black PLWH. Overall, participants assigned to the PATH intervention arm are assigned to receive support from one peer navigator and have access to the PATH webapp. Peer navigators meet with their clients at least monthly to deliver peer empowerment sessions. Empowerment sessions occur during the first 6 months, after which participants continue to have access to their peer and the PATH webapp for 12 months total, for example by messaging the peer through the PATH webapp. As much as possible, the study aims for peers to reflect the patient population by recruiting peers who speak English and Spanish, and who are Hispanic or Black. The PATH webapp is available in both languages. Translations of the webapp content were first translated then back-translated and reviewed for cultural and linguistic accuracy.

**Fig. 1 Fig1:**
[figure not shown]
Summary of PATH intervention features and the theory-informed mechanisms of action that are hypothesized to produce effects on the primary and secondary outcomes

#### Criteria for discontinuing or modifying allocated interventions {11b}

The outcome analysis will follow the intent-to-treat approach. Under no circumstances is it possible for the allocated intervention (i.e., usual care or PATH intervention) to be modified once the participant has been enrolled in the trial. However, participants may be unenrolled from the study at any point due to voluntary withdrawal for any reason.

#### Strategies to improve adherence to interventions {11c}

For participants randomized to the PATH intervention arm, a number of strategies are used to promote adherence to the intervention. These include intensive one-on-one training on how to use the PATH webapp and its features, including re-training upon request. Upon randomization to the intervention arm, participants are also asked to sign a client confidentiality agreement which outlines how PATH intervention participants can expect to receive professional, timely, respectful, and trustworthy peer support. Finally, whenever possible, all clients receive a “warm handoff” to immediately meet their assigned peer navigator over Zoom or in person following randomization into the PATH arm.

#### Relevant concomitant care permitted or prohibited during the trial {11d}

One of the study eligibility criteria is that participants must not currently be enrolled in any other program, intervention, or research study designed to improve HIV adherence or engagement in HIV care (regardless of intervention approach). While this is assessed during screening procedures, if a participant were to receive HIV care and/or ART adherence support from another program or research study during their participation in the trial, this information is recorded during follow-up assessments but does not require disenrollment from the trial.

#### Provisions for post-trial care {30}

Participants will not be provided any additional care outside of UC from the community-based FQHC.

### Outcomes {12}

The primary outcome in this trial is sustained viral suppression, defined as an HIV viral load at 6 and 12 months post-enrollment of less than 200 copies/mL. Secondary outcomes include the following variables: *Retention in HIV care* (at 6- and 12-month follow-up) is assessed through chart review using the HRSA definition of having greater than or equal to 2 HIV medical visits at least 90 days apart within the 12-month follow-up. *Gap in HIV medical visits* is measured through chart review at 6 and 12 months using the HRSA definition (no HIV medical visits in the last 6 months) [43]. *ART adherence* is measured using the self-report Wilson-3 scale [28] at 3-, 6-, 9-, and 12-month follow-up. The secondary outcomes were chosen to fill gaps in outcome measurements in the HIV peer navigation intervention literature [17] and to have a broader representation of the stages of engagement in the HIV care continuum [4].

### Participant timeline {13}

Interested participants meet with study staff (in person or over the phone) to complete a screening questionnaire. Once eligibility criteria are verified by study staff, the participant is asked to complete enrolment procedures within 30 days of completing screening. If 30 days have passed since the screening, the participants must be re-screened again to verify that they continue to be eligible for the study. Study enrolment procedures consist of the informed consent process, authorization to release personal health information for the research, completing a “locator” form to share details for future contact with the participants, and completing the baseline assessment through self-administration via an online survey tool (Qualtrics, Provo, UT). Only after these procedures have been completed, including the baseline assessment, are participants officially enrolled in the study and randomly assigned to either the control or the PATH intervention arm. Assignment to study arm is concealed to both study staff and participants until this final stage. A schematic of the participant timeline in the RCT is shown in Fig. 2.

**Fig. 2 Fig2:**
[figure not shown]
Schematic of participant timeline in the PATH RCT. *Participants are allowed to finish enrollment activities up to 30 days after they initially screen for eligibility, after which point they are required to re-screen. **Participants who are randomly allocated to the PATH intervention arm immediately complete intervention onboarding activities, which include assignment to their PATH peer navigator, creation of their account for the PATH web application, and in-depth tutorial on how to log into the PATH app and its features

### Sample size {14}

It was estimated that a sample size of up to 375 total participants would be required to achieve study objectives. This estimate was informed by a sample size calculation. Figure 3 displays power and sample size estimates based on intervention effect sizes and covariates. Meta-analytic data from Finitsis et al. [44] of mHealth text messaging interventions to promote ART adherence among PLWH has shown that such interventions can improve VL suppression (*k* = 3; OR = 1.57, 95% CI = 1.11, 2.20). This OR of 1.56 is a small effect size, and Chen et al. [45] established conventions of small, medium, and large ORs (similar to Cohen’s magnitudes of effect size, *d*). Based on the Finitsis meta-analysis (OR = 1.57), and accounting for other possible effect sizes of small (OR = 1.68) or medium (OR = 3.47) magnitude (based on Chen et al.) [45], the required sample sizes to achieve adequate power of at least 0.85 ranges from *n* = 179 to 204; with covariates in the model (accounting for 25% of the variance in the outcome, then a sample size ranging from *n* = 263 to 339 would be required). To provide further support for this power analysis, we conducted another analysis in G*Power using an effect size estimate from a recent peer navigation intervention (that does not include a mHealth component, “LINK LA” [46]) for HIV-positive men and transgender women released from jail. In this study, the investigators tested the efficacy of their peer navigation intervention compared to usual care (case management) and found a 22% difference-in-difference between the intervention and control arm on viral suppression over a 12-month follow-up. Using this effect size information, and assuming 0.80 power, alpha = 0.05, and 1:1 allocation ratio between intervention and control arms, the required sample size is 97 per group, or a total *n* of 194. Altogether, our calculations to estimate the desired sample size with adequate power and, based on up to 20% anticipated attrition, a sample size between 225 and 375 would provide us with adequate power to achieve our aims. Thus, our goal is to randomize up to 375 participants for an analytic sample size of ~ 300 (150 per arm).

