## Assignment of interventions: allocation

### Sequence generation {16a}

Enrolled participants are randomized on a 1:1 basis into the PATH intervention or usual care. Randomization is determined using an online generated randomization schedule determined prior to the study launch (a priori). Randomization is not stratified by substance use or race, although recruitment efforts are made to help ensure that at least a third of the sample are people with active substance use (defined as using non-prescription stimulants or opioids in the past 6 months) and that the sample is representative of the HIV patient population at the community-based FQHC (i.e., at least 60% Hispanic).

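### The sample sizes stated for 0.85 power are far too small for odds ratios of 1.57 and 1.68; at about 300 analysed, power for 1.57 is under 50%

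*Protocol article*

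**What the plan says.** The section Sample size {14} takes an odds ratio of 1.57 for viral suppression from a meta-analysis of text-messaging interventions, "accounting for other possible effect sizes of small (OR = 1.68) or medium (OR = 3.47) magnitude". For these effects it states that "the required sample sizes to achieve adequate power of at least 0.85 ranges from" 179 to 204. It adds that "with covariates in the model (accounting for 25% of the variance in the outcome, then a sample size ranging from" 263 to 339 would be needed.

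A second calculation uses a 22-point difference from a trial of peer navigation against case management, "assuming 0.80 power, alpha = 0.05, and 1:1 allocation ratio between intervention and control arms", and arrives at 97 per group (194 in total). With up to 20% attrition, the section concludes that 225 to 375 participants are adequate, and "our goal is to randomize up to 375 participants for an analytic sample size of" about 300, that is 150 per arm.

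Elsewhere the design is fixed as two arms: "Enrolled participants are randomized on a 1:1 basis into the PATH intervention or usual care" (Sequence generation {16a}). Under Statistical methods {20a}, sustained viral suppression is a yes/no outcome tested by regression at an alpha of .05. The text gives neither a control-arm suppression rate nor the sidedness of the test.

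**The concern.** Three features of the paragraph do not fit together, even before any control rate is assumed.

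- **Spread of the range.** Required sample size varies roughly with 1/(ln OR)². Between 1.57 and 3.47 it should change by (1.244/0.451)² = 7.6-fold. The stated range changes by 204/179 = 1.14-fold.
- **The two calculations conflict.** A 22-point difference corresponds to an odds ratio of at least 2.45 (the minimum, at 39% against 61%). The section says this needs 194 at 0.80 power. The much smaller effect of 1.57 cannot then need only 179 to 204 at the higher power of 0.85.
- **The plan misses its own upper figure.** A requirement of 339 exceeds the 300 to be analysed. With 20% attrition it means 339/0.8 = 424 randomised, above the cap of 375.

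The stake is how a null result is read. If the report says the trial had 0.85 power for 1.57 when it had less than an even chance, a missed effect of that size would be taken as lack of efficacy.

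**Working it through.** **Inputs.** Odds ratios 1.57, 1.68 and 3.47, power 0.85, alpha 0.05, 1:1 allocation, 300 analysed and 375 randomised are all from the protocol. Two-sided testing and the control rate are assumptions, so the rate is varied.

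**Trying to reproduce 179 to 204.** No two-arm calculation gives these figures. A logistic formula for a continuous, standard-normal predictor comes close. With event rate p,

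N = (z₀.₉₇₅ + z₀.₈₅)² / [p(1−p)(ln OR)²] = (1.960 + 1.036)² / [0.25 × 0.451²] = 176.5 at p = 0.50, and 210 at p = 0.30.

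A fuller version of the same calculation at a base rate of 0.50 gives 178 for 0.80 power and 203 for 0.85. Either way the odds ratio is then per standard deviation of a continuous variable with variance 1. A 1:1 arm indicator has variance 0.25, so the requirement is about four times larger: 4 × 176.5 = 706. This is a likely origin, not a proven one. The pair 263 and 339 was not reproduced by any single variant.

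**Two-arm calculation.** With control rate p₁, p₂ from the odds ratio, and p̄ their mean, the number per arm is

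n = [1.960√(2p̄(1−p̄)) + 1.036√(p₁(1−p₁) + p₂(1−p₂))]² / (p₂−p₁)².

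Example at p₁ = 0.50 and OR 1.57: p₂ = 1.57/2.57 = 0.611, the difference is 0.111 and p̄ = 0.555. Then n = [1.960 × 0.7027 + 1.036 × 0.6984]² / 0.1109² = 359 per arm, 718 in total.

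Power with 150 per arm is Φ[(0.1109√150 − 1.960 × 0.7027)/0.6984] = Φ(−0.03) = 0.489.

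| Control rate | Total N, OR 1.57 | Total N, OR 1.68 | Total N, OR 3.47 | Power for 1.57, N = 300 | Power for 1.57, N = 375 |
|---|---|---|---|---|---|
| 0.30 | 780 | 586 | 98 | 0.458 | 0.545 |
| 0.40 | 716 | 540 | 98 | 0.491 | 0.582 |
| 0.50 | 718 | 546 | 106 | 0.489 | 0.580 |
| 0.60 | 784 | 600 | 124 | 0.457 | 0.544 |
| 0.70 | 936 | 720 | 160 | 0.395 | 0.474 |
| 0.80 | 1282 | 994 | 234 | 0.304 | 0.366 |

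**Best case over control rates from 5% to 95%.**

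- OR 1.57 needs at least 710 (568 one-sided). OR 1.68 needs at least 538 (430 one-sided).
- Power for 1.57 is at most 0.32 at 179, 0.36 at 204, 0.44 at 263, 0.494 at 300, 0.54 at 339 and 0.585 at 375.
- Power for 1.68 is at most 0.45 at 204 and 0.61 at 300.

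**What 150 per arm does detect with 0.85 power.** An odds ratio of 2.0 to 2.1 (16 to 17 points) at control rates of 40 to 60%, and 2.3 at 70%.

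**Covariates.** The inflation 1/(1−R²) applies when the predictor of interest is correlated with the other covariates. Under randomisation, arm and baseline covariates are independent, so this R² is zero in expectation. Covariates that explain the outcome raise power rather than the required sample.

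**The 22-point figure.** The same formula at 0.80 power gives at most 80 per group (89 with continuity correction), against the stated 97. That error is on the safe side.

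**The case against.** **The plan rests on more than 1.57.** The 22-point effect comes from a peer-navigation trial, arguably nearer to this intervention than text messaging. It has about 97% power or more at 150 per arm for control rates of 30 to 70%. An odds ratio of 3.47 is also well covered: power is 0.89 or more even at 179 over those rates. This stands, and the restated section should say so. It does not rescue the claim for 1.57, which the section names first, or for 1.68.

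**The 300 may be pessimistic.** Under {20a}, a missing viral load counts as non-suppression, so all 375 could enter the primary analysis, and 375 exceeds 339. Power for 1.57 is still at most 0.585, and the rule also dilutes the effect. If 20% were missing in both arms (an assumption), 1.57 would shrink to between 1.25 and 1.47 at control rates of 40 to 80%, and power at 375 to between 18 and 43%.

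**The 50% line is close, and sidedness is not stated.** True: one-sided, the maximum is 0.62 at 300. Counting the 25% explained variance wholly as a precision gain gives about 0.61. Both remain far below 0.85.

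**Repeated measures might help.** The primary outcome is a single sustained yes/no, although {20a} also describes mixed models. Analysing the two visits as repeated binary measures at 300 gives about 56 to 68% power for within-person correlations of 0.7 down to 0.3. Only uncorrelated visits would halve the requirement, to about 710/2 = 355. That is still above 300, and independence of a person's two viral loads is not realistic.

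**The origin of the range is conjecture.** Agreed. If the range in fact spans power levels at one odds ratio, the fold-spread argument weakens. The finding does not depend on it: the bound of 710 holds at every control rate, so no further input in Figure 3 could restore the stated ranges.

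**Conclusion.** The concern holds. For a two-arm 1:1 comparison on a binary outcome, 179 to 204 and 263 to 339 do not give 0.85 power for odds ratios of 1.57 or 1.68 under any control rate, one-sided or two-sided. The two-sided shortfall for 1.57 is about 3.5-fold against the larger uncorrected figure (710/204) and 2.1-fold against the larger covariate figure (710/339).

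The statement that power is under 50% rests on two-sided 0.05 and the protocol's own 300 analysed. The statement that it is well below 0.85 does not depend on either. The trial is adequately powered for the 22-point difference and for 3.47, so the error lies in what is claimed for small effects.

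**What to change.** In Sample size {14} and Figure 3:

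1. Delete both ranges (179 to 204 and 263 to 339).
2. State the assumed control-arm rate of sustained suppression and the sidedness of the test.
3. Report what the design delivers at about 300 and at 375. For example: 150 per arm gives 0.85 power for an odds ratio of about 2.0 to 2.1 (16 to 17 points) at control rates of 40 to 60%; power for 1.57 is about 46 to 49%, or 54 to 58% if all 375 are analysed. Note that the 22-point difference has about 97% power or more at 300 for control rates of 30 to 70%.
4. Remove the statement that covariates explaining outcome variance increase the required sample.
5. Recompute the 97 per group, which is larger than the standard formula gives, or state the method behind it.

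The cost is rewording one section and redrawing one figure, and a less favourable power statement. Arms, endpoint, analysis and the target of 375 stay as they are.

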## Trial design {8}

We are implementing a two-arm parallel group randomized controlled superiority trial design, whereby enrolled participants complete a baseline assessment, and then are randomized on a 1:1 ratio into one of two arms. In the control arm, participants receive UC Ryan White coordinated case management services (i.e., standard intake and as needed, referrals medical, dental and mental health services, case management, and alcohol/substance use treatment]). In the PATH intervention arm, participants receive UC plus two main intervention components: (1) support from a peer navigation program and (2) access to the PATH mHealth web application. Post-baseline/randomization, participants are asked to complete follow-up assessments at 3, 6, 9, and 12 months.

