The primary analytic approach will utilize generalized mixed-effects models and an intent-to-treat (ITT) approach. This addresses issues with attrition, missing data, and other unintended violations of design, thereby allowing us to maximize statistical power by not excluding subjects with some missing data. Mixed-effects models incorporate random intercepts and slopes for each participant based on the participant’s multiple measurements over time [65]. Intra-class correlations among participants nested within specific peer navigators will be examined to diagnose whether significant variation in outcomes is explained by the shared peer navigator, if so, models will account for clustering. Attrition analyses will compare participants who complete all measurements to those who do not based on baseline characteristics. If there is a baseline imbalance between participants retained in the study versus not across certain characteristics, then these will be accounted for in all analyses. In addition, maximum likelihood will be used to address incomplete data because this makes the relatively mild assumption that missing data are conditionally missing-at-random [66]. Outcome analysis will apply a priori planned comparisons. It is hypothesized that compared to control, participants in the PATH intervention will exhibit the following: greater viral suppression at 6- and 12-month follow-up (HYP 1); greater retention in care (HYP 2); fewer gaps in HIV care (HYP 3); greater ART adherence (HYP 4). HYP 1–3 involve binary outcomes (Y/N on sustained viral suppression, retained in care, had gaps in care), while HYP 4 is a continuous outcome (proportion). These hypotheses will be tested using regression analysis specifying the appropriate outcome distribution (e.g., binomial) and function (e.g., logit), with *α* = .05; any subsequent post-hoc comparisons will be adjusted via simulation-based stepdown methods [67] to maintain a nominal type 1 error rate of .05. For the primary outcome sustained viral suppression, we will assume non-suppression at that time point (6 or 12 months) for any missing viral load chart data. A sensitivity analysis will be conducted utilizing only available viral load chart data to compare with the results assuming missing viral load equals non-suppression.

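### The increase in required sample size from 179–204 to 263–339, attributed to covariates explaining 25% of outcome variance, is unsupported for a 1:1 randomised comparison

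*Protocol article*

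**What the plan says.** Sample size {14} of the protocol article takes an odds ratio of 1.57 from a meta-analysis of text-messaging interventions, "accounting for other possible effect sizes of small (OR = 1.68) or medium (OR = 3.47) magnitude". It then states that "the required sample sizes to achieve adequate power of at least 0.85 ranges from *n* = 179 to 204". The next clause gives a larger figure for an adjusted model: "with covariates in the model (accounting for 25% of the variance in the outcome, then a sample size ranging from *n* = 263 to 339 would" apply. A separate calculation from a peer-navigation trial gives 194 in total. With up to 20% attrition, the section arrives at 225 to 375 and sets a goal of up to 375 randomised for about 300 analysed.

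On design and analysis, Trial design {8} says participants complete baseline and "then are randomized on a 1:1 ratio into one of two arms". Statistical methods {20a} says "These hypotheses will be tested using regression analysis specifying the appropriate outcome distribution (e.g., binomial) and function (e.g., logit" are to be specified, and treats sustained viral suppression as a yes/no outcome. The same section provides for covariate adjustment where arms are imbalanced or where characteristics relate to attrition.

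**The concern.** The reason given for the larger sample is variance explained in the outcome. In regression sizing, a penalty for covariates comes from correlation between the covariates and the predictor of interest. Here that predictor is study arm, which randomisation makes independent of baseline covariates in expectation. Variance explained in the outcome is a different quantity and does not enter that penalty.

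A stated required sample size is therefore attached to a reason that cannot produce it. It is also the only printed range that contains the analysed target, so a reader who tries to reconstruct the target has to rely on it. If the sizing is redone and the same step is carried over, the error goes with it.

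**Working it through.** **Inputs from the documents.** Base n 179–204 at power of at least 0.85; n with covariates 263–339; covariate share 25% of outcome variance; odds ratios 1.57, 1.68 and 3.47; 1:1 randomisation; alpha 0.05; attrition 20%; 375 randomised, about 300 analysed.

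**Assumptions, not in the documents.** Two-sided test. One independent baseline covariate with latent R² = 0.25, that is variance (0.25/0.75) × π²/3 = 1.097 on the logit scale. Suppression probability of 0.50 to 0.62 for a control participant at the covariate median.

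**1. Can the printed increase be reproduced?** The inflation is n/(1−R²), with R² the share of the arm indicator explained by covariates.
- R² about 0 (randomised arm): factor about 1, no increase.
- R² = 0.25 misapplied: 179/0.75 = 239 and 204/0.75 = 272, not 263 and 339.
- Pairing the ends of the ranges gives 263/179 = 1.47 and 339/204 = 1.66, implying R² of 1 − 179/263 = 0.32 and 1 − 204/339 = 0.40. The pairing is assumed, but 339 is at least 1.66 times any value in the base range.

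**2. What does a prognostic covariate do in a logistic model?** Let K = (1.960 + 1.036)² = 8.98, and read the listed odds ratio as conditional on the covariate. Total N for power 0.85, using the variance of the arm log odds ratio throughout:
- Homogeneous population: N = K[2/(p0(1−p0)) + 2/(p1(1−p1))]/ln(OR)². For OR 1.57 and p0 = 0.50, p1 = 0.611: 8.98 × 16.41/0.2035 = 724.
- Covariate present, unadjusted: same formula with rates averaged over the covariate. These are 0.500 and 0.591, marginal ln(OR) 0.368: 8.98 × 16.27/0.1354 = 1079.
- Covariate present, adjusted: N = K × V/ln(OR)², with V from the Fisher information averaged over the covariate. V = 20.08: 8.98 × 20.08/0.2035 = 886.

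| OR | Median control rate | Homogeneous | Unadjusted | Adjusted | Adjusted/unadjusted | Adjusted/homogeneous |
|---|---|---|---|---|---|---|
| 1.57 | 0.50 | 724 | 1079 | 886 | 0.82 | 1.22 |
| 1.57 | 0.62 | 812 | 1144 | 947 | 0.83 | 1.17 |
| 1.68 | 0.50 | 552 | 819 | 674 | 0.82 | 1.22 |
| 1.68 | 0.62 | 624 | 873 | 725 | 0.83 | 1.16 |
| 3.47 | 0.50 | 113 | 157 | 134 | 0.86 | 1.19 |
| 3.47 | 0.62 | 140 | 176 | 152 | 0.86 | 1.09 |

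The adjusted test needs 14–18% fewer participants than the unadjusted test in the same population. If the unadjusted test is sized with the pooled-variance two-proportion formula instead, the saving at OR 3.47 shrinks to about 9–10%; the direction does not change.

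**3. How does the range relate to the target?** Allowing for 20% attrition:
- 179/0.8 = 224, 194/0.8 = 243 and 204/0.8 = 255.
- 375 × 0.8 = 300, which lies inside 263–339.
- 339/0.8 = 424, above the 375 maximum.

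**4. Is the base sound?** It does not reproduce as a two-arm comparison. Over control rates of 0.10 to 0.90, two-sided totals for power 0.85 are at least 716 for OR 1.57 and at least 540 for OR 1.68. For OR 3.47 they are 98 to 160 at control rates of 0.3 to 0.7. A figure near 179 appears if arm is treated as a standard-normal predictor with OR 1.57 and event rate 0.5: 8.98/(0.25 × 0.2035) = 177.

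**The case against.** The strongest counter-argument is that the effect of adjustment on n depends on which odds ratio is meant. The section applies the same listed odds ratios to two scenarios, without and with covariates. If the odds ratio in the second scenario is conditional, n does rise relative to a population with no covariate effect. This stands, and it rules out the flat statement that covariates can never raise n in a logistic sizing. It does not rescue the printed figures: the rise is at most about 1.22 times over the assumed control rates, against 1.47 to 1.66.

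Four stronger readings go beyond the documents.
- A reader might convert the two ranges into a loss of power at a fixed n. The section prints no such loss, gives power only as a minimum, and does not say which base goes with which covariate figure.
- A reader might say the covariate range determined the target. The text says only that the calculations were taken together, and the upper end was not followed.
- A reader might say the section argues against adjustment. Statistical methods {20a} provides for it.
- A reader might conclude that the trial is larger than it needs to be. The base calculation rules that out.

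Figure 3 is not available here and may show further settings. It could not turn outcome variance explained into a reason for the 1/(1−R²) inflation under randomisation.

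**Conclusion.** The 263–339 range is unsupported. Its stated reason does not justify an increase through the usual inflation, and its size does not follow from 25% by that route (239–272) or by the conditional odds ratio reading (at most about 1.22 times). These statements about size rest on a single independent covariate with latent R² 0.25 and an assumed median control rate of 0.50–0.62. The absence of the 1/(1−R²) inflation rests only on 1:1 randomisation.

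The target of about 300 appears to draw on this range, because no other printed requirement inflates beyond 255 randomised, but this is inferred. The point says nothing in favour of a smaller trial. With 150 per arm and control rates of 0.40 to 0.64, unadjusted two-sided power is about 0.44–0.49 for OR 1.57 and 0.54–0.61 for OR 1.68. If those values are conditional odds ratios in a population with such a covariate, simulation (4,000 trials per setting, control rate about 50%) gives 0.36 unadjusted and 0.42 adjusted for OR 1.57, and 0.45 and 0.52 for OR 1.68. Adjustment helps, but it does not bring the two smaller effects to 0.85.

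**What to change.** Remove the 263–339 figures and recalculate the 179–204 base in the same revision, so that 179–204 is not left as the surviving sizing. State the control-arm rate of sustained suppression, the sidedness of the test, a binary arm indicator, and whether each odds ratio is marginal or conditional. Report power at 300 analysed for OR 1.57, 1.68 and 3.47, unadjusted and covariate-adjusted, with no covariate inflation of n. If the 25% is kept, say that it is outcome variance explained and let it enter only through the adjusted power.

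The cost is one recalculation and a few lines in Sample size {14}, with Figure 3 updated to match. This restatement does not itself change trial conduct.
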